### 3.5 Research phases and tools

This research protocol details the development, implementation, and evaluation of the InTroDuce-Programme, aimed at enhancing knowledge and increasing the future uptake of Influenza and Tdap vaccination among pregnant mothers. The study is divided into three sequential phases to ensure a comprehensive and systematic approach:

#### Phase 1: Needs Assessment

The first phase focuses on collecting essential information to guide the development of the intervention module, including:

1. **Literature Review:** A review on the existing research related to vaccine acceptance, hesitancy, and awareness among pregnant women to identify the knowledge gaps and factors associated with vaccine uptake will be conducted.
2. **Quantitative Study/Survey:** A baseline survey will be conducted to determine the target population's knowledge, attitudes, and agreement toward vaccine uptake.
3. **Guideline Review:** A detailed appraisal on the international and local vaccination guidelines with insights from the subject matter experts will be conducted to ensure the intervention align with evidence-based practices guidelines.

## **Phase 2: Development of the Interventional Educational Module**

The second phase emphasizes the design and refinement of the educational module through an iterative process:

1. **Content and Theory Development:** The theoretical framework will be use in establishing key educational messages to ensure the module is well structured and impactful.
2. **Module Drafting:** Creating initial interventional materials, including text and visual components to address vaccine safety, efficacy, importance and common misconceptions related to vaccine.
3. **Expert Review and Content Validation:** Engaging subject matter experts like family medicine specialists, obstetricians and public health specialist to provide feedback and validate the scientific accuracy and relevance of the content.
4. **Refinement:** Revising the intervention educational module based on expert recommendations to enhance the clarity, accuracy and practicality.
5. **Method Selection:** Identifying practical methods for delivering the module (e.g., using WhatsApp as the digital platforms) and mechanisms for assessing its impact will be conducted using google form.
6. **Pilot Study:** Testing the module with a small group of pregnant women to identify practical and logistical challenges, as well as gathering participant feedback in terms of clarity of the questionnaire and the feasibility of the study.
7. **Module Evaluation:** A systematic evaluation based on Context, Input, Process, and Product (CIPP) of the educational model will be conducted.
8. **Final Refinement:** Incorporating feedback from the pilot study and module evaluation will be used to produce the finalized version of the intervention educational module.

## **Phase 3: Implementation and Effectiveness Measurement**

The final phase involves the intervention implementation and evaluating its effectiveness through a randomised control trial (RCT):

1. **Study Design:** A cluster RCT will be used to compare the effectiveness of the **InTroDuce-Programme** (intervention group) versus standard care (control group) in improving the future vaccine uptake.
2. **Outcome Measurement:**
3. The module's effectiveness will be assessed using pre- and post-intervention questionnaires:
  1. **Primary Outcome:** Improvement in participants' knowledge of vaccination safety, benefits, and future uptake intentions.
  2. **Secondary Outcomes:** Identification of barriers to vaccination uptake and socio-demographic factors influencing outcomes.

### **Questionnaire (Appendix B)**

A validated questionnaire will be used in this study to measure vaccine-related knowledge, attitude and future uptake intention. The questionnaire will be adapted from a study conducted by Hong et al in Singapore (7). There are 6 sections in this questionnaire.

Part A: 3 questions for screening purposes to exclude respondents who did not fulfill the inclusion criteria.

Section 1: 9 items on sociodemographic data and the health status of the respondents.

Section 2: 4 items to assess the knowledge on vaccination in pregnancy.

Section 3: 5 items to assess the knowledge about whooping cough.

Section 4: 4 items to assess the knowledge on Influenza Infection.

Section 5: 2 items to assess attitude towards vaccination in general and in pregnancy.

Section 6: 6 items to assess attitude towards vaccination against influenza and whooping cough during pregnancy.

Content and face validity will be conducted among six experts on the questionnaires.

### **3.6 Data Collection**

- **Knowledge and attitude Assessment:** A pre- and post-intervention questionnaire will assess knowledge about the importance, safety, and benefits of vaccination (vaccine literacy)

- **Vaccination future uptake:** Intention of future vaccine uptake of the influenza and Tdap vaccines will be assessed using questionnaire
- **Follow-up:** Participants will be followed up at one month after providing intervention to assess intention of future vaccine uptake and barriers if not intending for vaccination uptake

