### **Specific objectives:**

- 1) To determine the sociodemographic factors and clinical variables among study population.
- 2) To determine the prevalence of future vaccination uptake following the InTroDuce-Programme.
- 3) To evaluate the level of participants' attitudes and barriers towards future vaccination uptake before and after the InTroDuce-Programme.
- 4) To determine the effectiveness of the InTroDuce-Programme in improving knowledge and future uptake of influenza and Tdap vaccination among pregnant mothers.
- 5) To determine the factors associated with low future uptake of vaccine with socio-demographic factors (age, race, income, education) among pregnant mothers.

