#### 3.3.2 Exclusion Criteria

1. Pregnant women with severe anaphylactic or allergic reactions to previous dose of influenza or Tdap vaccination.
2. Non-Malaysian

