### **3.9 Statistical Analysis Plan**

#### **Statistical Methods:**

- a. Primary outcome (knowledge score) will be analyzed using paired t-tests or Mann-Whitney U tests for non-parametric data.
- b. Secondary outcomes (vaccination uptake which is yes or no) will be analyzed using multiple logistic regression to determine the factors associated with no vaccination uptake intention.

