#### **Benefits:**

1. Participants in the intervention group will gain valuable knowledge about influenza and Tdap vaccination, potentially increasing their confidence and willingness to vaccinate.

2. By choosing vaccination during the study, participants may lower their own risk of severe influenza or pertussis and protect their newborns.
3. Participants contribute to improving the understanding of barriers and facilitators of vaccination, which could benefit future pregnant women and public health programs.

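### The outcome labelled vaccination uptake is collected only as stated intention, and women vaccinated before the one-month follow-up have no defined category

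*Protocol*

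**What the plan says.** **What is collected.** Section 3.6 defines future uptake as a questionnaire item on intent: "Intention of future vaccine uptake of the influenza and Tdap vaccines will be assessed using questionnaire". The one-month follow-up in the same section is there "to assess intention of future vaccine uptake and barriers if not intending for vaccination uptake". Section 3.8 (Visit 3) likewise lists knowledge, attitudes and intention. The questionnaire description in section 3.5 lists screening, sociodemographic and health-status, knowledge and attitude items. No section of it is described as covering receipt of a vaccine.

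**What is analysed.** Section 3.9 says: "Secondary outcomes (vaccination uptake which is yes or no) will be analyzed using multiple logistic regression". The variable is described as "vaccination uptake which is yes or no", yet the same sentence gives the purpose of the model as "to determine the factors associated with no vaccination uptake intention".

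**What is to be concluded.** Specific objective 2 reads "To determine the prevalence of future vaccination uptake following the InTroDuce-Programme". Objective 4 asks whether the programme improves future uptake, and objective 5 asks for factors associated with low future uptake.

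**Who may be vaccinated by the follow-up.** The Benefits text in section 3.10 says: "By choosing vaccination during the study, participants may lower their own risk of severe influenza or pertussis and protect their newborns". The Risk text there also anticipates women who choose to be vaccinated. Section 3.3.2 lists two exclusions, non-Malaysian status and "Pregnant women with severe anaphylactic or allergic reactions to previous dose of influenza or Tdap vaccination". Women already vaccinated in this pregnancy are therefore eligible.

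**The concern.** Two things are at stake.

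The first is what the trial can claim. A statement of intent at one month does not show that anyone was vaccinated. A report that follows the label in section 3.9 would claim more than the data show.

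The second is classification. A question about future intent does not fit a woman who has already had the vaccine. If she answers no, which would be truthful, she is grouped with women who refuse. That would affect three results:

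- the between-arm comparison required by objective 4;
- the barrier items, which section 3.6 directs to women who do not intend vaccination;
- the regression in section 3.9, whose event is lack of intention.

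If the programme works quickly, more women in the intervention arm will be in this position, so the error would tend to work against the programme. It cannot be repaired at the analysis stage if receipt was never recorded, so a separate analysis plan would not remove it.

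**Working it through.** **Step 1. The texts side by side.** Sections 3.6 and 3.8 collect intent. Section 3.9 labels the variable uptake and models lack of intention. Section 3.10 foresees vaccination during the study. Section 3.3.2 admits women already vaccinated. No section plans to record receipt or assigns vaccinated women to a category.

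**Step 2. The plan's own sample size.** Inputs from section 3.4: 36% and 55%, two-sided 5% level, 80% power, 1:1 allocation, design effect 1.3, non-response 20%. With mean proportion 0.455, the uncorrected formula gives

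n per arm = [1.96·√(2·0.455·0.545) + 0.842·√(0.55·0.45 + 0.36·0.64)]² / 0.19² ≈ 107.

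The protocol shows 108, a total of 216. Then 216 × 1.3 = 280.8, taken as 281, and 281 / 0.80 = 351.25, stated as 351. The figure reproduces, so this point does not rest on an arithmetic error.

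**Step 3. Illustration of the miscount.** Assume that 55% and 36% are the true proportions 'vaccinated or intends'. Let f₁ (intervention) and f₀ (control) be the shares of these positive women who were vaccinated before follow-up and answer no. The observed difference is

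0.55·(1 − f₁) − 0.36·(1 − f₀).

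Approximate power uses 108 effective women per arm, which is 351 × 0.80 / 1.3 / 2, and

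z = [d·√108 − 1.96·√(2·p̄·(1 − p̄))] / √(p₁(1 − p₁) + p₀(1 − p₀)).

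| f₁ | f₀ | Observed rates | Difference (points) | Power |
|---|---|---|---|---|
| 0 | 0 | 55.0% vs 36.0% | 19.0 | 80.5% |
| 10% | 5% | 49.5% vs 34.2% | 15.3 | 63% |
| 20% | 10% | 44.0% vs 32.4% | 11.6 | 42% |
| 20% | 20% | 44.0% vs 28.8% | 15.2 | 64% |

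The last row shows that unequal shares are not needed: an equal share in both arms also shrinks the difference, because it removes the same fraction of a larger proportion.

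**Step 4. Could the sign change?** With f₀ = 10%, the observed difference reaches zero only when f₁ = 1 − 0.36 × 0.90 / 0.55 = 0.41. About 41% of positive women in the intervention arm would have to be vaccinated and answer no. Nothing in the protocol points to a share of that size.

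**The case against.** **Intention is disclosed.** The Synopsis, Phase 3 in section 3.5, the questionnaire description and sections 3.6 and 3.8 all say intention, and the sentence in section 3.9 itself ends on intention. A reader might infer that the protocol passes intent off as receipt. It does not: the term uptake is used loosely, mainly in section 3.9 and the objectives. Intention is a legitimate endpoint for an education trial with one month of follow-up. This part of the objection stands, so on this count the matter is one of consistent naming.

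**The item wording is unseen.** Appendix B is not shown. Its response options might include one for women already vaccinated. This stands too. A reader might infer that vaccinated women will be recorded as failures, but the protocol contains no such rule. What remains is a risk that no visible text closes.

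**One yes/no for two vaccines.** The phrase in section 3.9 might suggest that influenza and Tdap are merged into one variable. The documents do not establish this. Section 3.6 names both vaccines, section 3.9 speaks of outcomes in the plural, and six attitude items cover both diseases.

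**The size is assumed.** The protocol gives no share of women vaccinated within a month. Section 3.10 shows that vaccination is possible, not that it is frequent. Section 3.4 does not say whether 55% and 36% refer to intention or receipt. The figures above are therefore illustrations only.

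**The remedy mixes behaviour and intent.** An outcome of 'received or intends' does not by itself support a claim about uptake. That is correct, and it is why the two components need separate reporting.

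**Conclusion.** The point holds in a limited form. The protocol labels as uptake an outcome that it collects as intention. It leaves without a category women whom it allows to enrol already vaccinated, or expects may be vaccinated before follow-up. If Appendix B does not deal with them, they can be counted with non-intenders in the arm comparison, the barrier items and the factor model.

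The likely consequence is attenuation of the programme's effect. Under the assumed shares, the planned 19 points become 15.3 (10% vs 5% miscounted) or 11.6 (20% vs 10%), and power falls from about 80% to about 63% or 42%. These results depend on the assumed shares, on reading 55% and 36% as 'vaccinated or intends', and on the protocol's own design effect and non-response rate.

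A reversed effect might be inferred, but none of these scenarios produces one, and it would need a share near 41% in the intervention arm. The matter should be settled before data collection, because receipt that is not recorded cannot be recovered in the analysis.

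**What to change.** 1. Add one item per vaccine, at baseline and at one month, asking whether it has already been received in this pregnancy.
2. For each vaccine, define the outcome as 'received since baseline or intends to receive' versus neither. Report the two components separately.
3. Omit from a vaccine's analysis women who had received that vaccine before baseline.
4. Direct the barrier items, and define the event in the section 3.9 model, according to the 'neither' category.
5. Write 'vaccination intention' in section 3.9, the objectives and the conclusions wherever receipt is not measured.
6. State in section 3.4 whether 55% and 36% refer to intention or receipt, so that the planning rates match the chosen outcome.

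The cost is two short questionnaire items, some rewording and a somewhat smaller analysed sample per vaccine. The protocol gives no figure for the last. If 10% of women had received a vaccine before baseline (an assumption), the 281 expected respondents would become 281 × 0.90 ≈ 253 for that vaccine.

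### The protocol conflicts on when and from whom barriers to vaccination are collected; as Section 3.6 reads, a baseline value is not assured and follow-up covers only women who do not intend to vaccinate

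*Protocol*

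**What the plan says.** Three places in the protocol bear on barriers.

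- **Section 2.0, specific objective 3** (repeated in the Research Synopsis): "To evaluate the level of participants' attitudes and barriers towards future vaccination uptake before and after the InTroDuce-Programme".
- **Section 3.5, Phase 3.** The outcome list is introduced by "The module's effectiveness will be assessed using pre- and post-intervention questionnaires", and the secondary outcomes under it read "Identification of barriers to vaccination uptake and socio-demographic factors influencing outcomes". Nothing there limits barriers to a subgroup.
- **Section 3.6, Data Collection.** The follow-up item says that women are contacted one month after the intervention "to assess intention of future vaccine uptake and barriers if not intending for vaccination uptake". This is the only sentence that says when, and of whom, barriers are asked.

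The other operational text does not mention barriers. Section 3.6 describes the pre/post instrument as follows: "A pre- and post-intervention questionnaire will assess knowledge about the importance, safety, and benefits of vaccination (vaccine literacy"; the label of that item adds attitude. Section 3.5 (Questionnaire) gives the instrument's purpose as "to measure vaccine-related knowledge, attitude and future uptake intention" and lists sections on screening, sociodemographics, knowledge and attitude. The listed section most likely to touch on barriers is "6 items to assess attitude towards vaccination against influenza and whooping cough during pregnancy". Section 3.8 has a pre-intervention survey at Visit 1 without stating its content, and at Visit 3 names knowledge, attitudes and intention.

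**The concern.** A before-and-after statement needs the same quantity measured at both times in the same women. The rule in Section 3.6 secures one time point and one subgroup. A team that builds its forms from Section 3.6 would hold no baseline barrier value and no follow-up value for any woman who says she intends to be vaccinated.

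The subgroup is also not neutral. Intention at one month is measured after allocation and is what the programme is meant to change. The women asked about barriers in the intervention clinics are therefore those whom the programme did not persuade, and they need not resemble the control women who are asked.

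This has to be settled in the protocol and the forms. A statistical analysis plan can choose among analyses, but it cannot supply answers that were never requested.

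**Working it through.** **1. The passages side by side**

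| Place | When | From whom |
|---|---|---|
| Section 2.0, objective 3 | Before and after | Participants, no restriction |
| Section 3.5, Phase 3 | Pre and post questionnaires | No restriction |
| Section 3.6, follow-up item | One month | Only women not intending to vaccinate |
| Section 3.5, Questionnaire | Not stated | No section labelled barriers |
| Section 3.8, Visits 1 and 3 | Barriers not named | Barriers not named |

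The first two rows agree with each other and conflict with the third. The last two do not resolve the conflict.

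**2. The plan's own sample size (context only)**

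Inputs from Section 3.4: 55% against 36%, two-sided 5%, 80% power, design effect 1.3, 20% non-response. The standard two-proportion formula gives 107 per arm, close to the 108 per arm (216 in total) in the protocol's table. Then 216 × 1.3 = 280.8, rounded to 281, and 280.8 / (1 − 0.20) = 351. The stated 351 reproduces. The point about barriers does not depend on it.

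**3. How many women would be asked**

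Assumptions: the 55% and 36% apply as one yes/no intention rate at one month, and 281 women are evaluable in equal arms (140.5 each).

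- Intervention: 140.5 × (1 − 0.55) = 63.2, about 63 women (45%).
- Control: 140.5 × (1 − 0.36) = 89.9, about 90 women (64%).
- Together: 153.1 of 281 = 54.5%. About 128 women would not be asked.

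If all 351 responded (175.5 per arm), the counts would be 79 and 112, with the same percentages.

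**4. What selection alone can do**

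Suppose a given barrier is held by a share p of control non-intenders. Suppose also that the programme moves 19% of women (55 − 36) to intending and changes nobody's barrier. Let s be the share of those persuaded women who hold the barrier. Then

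share among intervention non-intenders = (0.64p − 0.19s) / 0.45.

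With p = 50% (an assumption), 0.64 × 0.50 = 0.32, and:

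- s = 0: 0.32 / 0.45 = 71%
- s = 0.5: (0.32 − 0.095) / 0.45 = 50%
- s = 1: (0.32 − 0.19) / 0.45 = 29%

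The control figure is 50% throughout. For any p the two arms agree only when s = p, that is, when the persuaded women hold the barrier as often as control non-intenders do. Otherwise a difference appears although no barrier has changed, and its sign depends on whom the programme persuades.

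**The case against.** The strongest reply is that Section 3.6 describes what happens at follow-up and does not say that barriers are left out at baseline. Section 3.5 (Phase 3) puts barriers under pre- and post-intervention questionnaires. The section labels of the questionnaire are not exhaustive either: its stated purpose includes intention, yet no listed section carries that label. Reasons and barriers could sit among the eight attitude items (2 in Section 5 and 6 in Section 6 of the questionnaire), and Appendix B is not shown. This stands. A reader might infer that barriers are certainly absent at baseline, and the document does not establish that. What it shows is that a baseline value is not assured. The Phase 3 text does not remove the conflict, because it states an intention that the only collection rule does not carry out.

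A reader might also infer that objective 3 as a whole fails. It does not: attitude has questionnaire items, is named in the label of the pre/post assessment in Section 3.6, and is assessed at Visit 3.

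A third tempting reading is that the protocol plans a biased comparison of arms on barriers. It states no such comparison. Objective 3 is worded as before and after, the secondary outcome is identification, and Section 3.9 gives no test of barriers between arms. Asking non-intenders for their reasons is a legitimate descriptive use. The selection problem arises only if the arms are compared within that subgroup. Such a comparison is a natural step, because Phase 3 introduces these outcomes as measures of effectiveness within a cluster randomised trial.

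Finally, the 55% and 36% are proportions from the cited study, used for sample size. There are two vaccines, and a woman may intend one and not the other, so the counts above are illustrative.

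**Conclusion.** The concern holds as an internal conflict among Sections 2.0, 3.5 and 3.6 on when and from whom barriers are collected. If Section 3.6 is followed as written, the barrier half of objective 3 cannot be answered, and follow-up barrier data exist only in women selected on a post-randomisation outcome. This rests on the protocol text alone, with one reservation: the unseen attitude items may cover barriers in part.

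The illustration of 63 against 90 women asked rests on treating the sample-size proportions as a single intention rate with 281 evaluable. The range of 29% to 71% against 50% rests on the further assumption that half of control non-intenders hold the barrier. It shows that a comparison within the subgroup could mislead in either direction; it does not predict a bias of known sign.

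A secondary outcome and one stated objective are affected. The knowledge outcome and the sample size are not. The change should be made before the questionnaires are used, because the missing answers cannot be recovered afterwards.

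**What to change.** **Preferred.** Amend Section 3.6, and align Sections 3.5 and 3.8, so that the same barrier items are asked of every participant in both arms at baseline and at one month, whatever her stated intention. If attitude items in Appendix B already serve this purpose, name them as the barrier measure. Keep the reasons given by non-intenders as a descriptive table. The cost is a few more items and slightly longer questionnaires at two contacts that are already planned; no visit is added and the sample size does not change.

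**Otherwise.** Remove the before-and-after claim for barriers from objective 3 (in Section 2.0 and the Synopsis), describe barriers as a descriptive outcome among women not intending to vaccinate, and state that arms will not be compared on them. This costs only wording, but gives up the barrier half of the objective.
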